## Treatment Assignment

- All patients will be offered home hospitalization.
- If patient/caregiver does not consent, the research assistant will ask the patient's permission to collect covariates, functional status, and a quality of life measure to determine generalizability of enrollment.

As an amendment to our current protocol, patients will be randomized (random sized blocks between 3 and 6 stratified by infection, heart failure, COPD/asthma, and other with concealed allocation) to remote care (intervention) versus in-person care (control) at the time of enrollment. Once 210 patients have been enrolled in this schema (see power calculations below), and if remote care is noninferior to in-person care, we will allow remote care to continue as a single arm while continuing other concurrent experiments.

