#### Covariates of Interest

| Measure                                      | Source                  | Day(s) Obtained |
|----------------------------------------------|-------------------------|-----------------|
| Age                                          | RA via EHR a | Admission       |
| Gender                                       | RA via EHR              | Admission       |
| Race/ethnicity                               | RA via patient          | Admission       |
| Primary language                             | RA via EHR              | Admission       |
| Health insurance status, public/private/none | RA via EHR              | Admission       |
| BMI                                          | RA via EHR              | Admission       |

|                                                               |                         |                |
|---------------------------------------------------------------|-------------------------|----------------|
| Comorbidities, type and #                                     | RA via EHR and H&P      | Admission      |
| Partner status                                                | RA via patient          | Admission      |
| Education                                                     | RA via patient          | Admission      |
| Zip code                                                      | RA via EHR              | Admission      |
| Employment                                                    | RA via H&P              | Admission      |
| Smoking status                                                | RA via H&P              | Admission      |
| Medications used as outpatient, #                             | RA via EHR              | Admission      |
| DNR/I code status                                             | RA via H&P              | Admission      |
| Home health aide prior to admission                           | RA via patient          | Admission      |
| Readmission risk score on discharge (HOSPITAL)                | RA via EHR              | Discharge      |
| Elective and urgent admissions in the previous year, #        | RA via EHR and patient  | Admission      |
| ED visits in the previous 6 months, #                         | RA via EHR and patient  | Admission      |
| Interqual disease-specific leveling                           | RN                      | Admission      |

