## Statistical methods

### *Home hospital vs traditional hospital*

#### *Quantitative*

We plan to form 3 different control groups (with groups listed in order of preference):

1. Patients who were deemed eligible for home hospital, but the service was full (and they were not enrolled subsequently if the service was no longer full);
2. Patients who were deemed eligible for home hospital, but lived outside of the 7.5-mile catchment area; and
3. Patients who were admitted to the hospital.

For each control group, we will use propensity score weighting, adjusting for covariates of interest (see table above), baseline functional status, and DRG. We will be cognizant of over-adjustment depending on our final sample size for each group above. If possible, we will use only group 1 above, as it is the strongest. If we have insufficient control group sample size, we may choose to combine groups 1 and 2 above.

The primary outcome (hospitalization cost) will be assessed using a generalized linear model assuming a gamma distribution with a log link. We will use a multivariable regression approach for secondary

outcomes, using logistic regression for binary outcomes and non-transformed linear regression for normally distributed continuous outcomes as appropriate.

We *a priori* plan to perform a subgroup analysis that does not involve any outlier participants, should this occur. We also *a priori* plan subgroup analyses by diagnosis, by age group, by disposition, by location of admission (e.g., ED, floor, clinic, and home), and by daily activity level. We also *a priori* plan to analyze our outcomes with means, but also with median and interquartile ranges, which are less subject to outlier effects. We may choose to employ non-parametric tests of significance should our data be nonparametric.

We *a priori* plan to adjust our secondary analyses using the Benjamini-Hochberg method. We *a priori* choose a false-discovery rate of 0.20.

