### *Remote vs In-Person Physician Care*

In a randomized controlled non-inferiority trial, we will test an in-person daily physician visit (“in-person care;” control) vs a daily physician visit conducted remotely via video facilitated by a care team member (“remote care;” intervention) for acutely ill patients who are home hospitalized. The primary outcome (dependent variable) is number of adverse events during the acute episode of care (see “Summarizing Adverse Events” table below). The primary predictor (independent variable) is study arm (in-person care vs remote care). We will assess the non-inferiority of the primary outcome with a generalized linear model using Poisson distribution, given the primary outcome is count data. Although we have multiple covariates of interest, we are cognizant of over adjustment. We plan to adjust for age, gender, race/ethnicity, PRISMA-7, education, and HOSPITAL score). We may include additional covariates if groups have significant differences at baseline.

Because patients in the intervention arm will receive at least some of their intervention through a “change agent” (in this case, a Home Hospital team) shared with other participants, we need to account for this in the analysis. We will therefore cluster by Home Hospital physician using general estimating equations.

Other outcomes will be analyzed in a similar manner, using Poisson regression for other “count” outcomes (e.g., number of new or worsening signs or symptoms per patient, days at home since discharge), multivariable logistic regression for binary outcomes (e.g., 30-day readmission, ED visit, PCP

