#### Summarizing Adverse Events

| Measure                                     |
|---------------------------------------------|
| Fall                                        |
| Delirium                                    |
| Potentially preventable VTE                 |
| New pressure ulcer                          |
| Thrombophlebitis at peripheral IV site      |
| CAUTI                                       |
| New Clostridium difficile                   |
| New MRSA                                    |
| New arrhythmia                              |
| Hypokalemia                                 |
| Acute kidney injury                         |
| Transfer back to hospital                   |
| Mortality (unplanned) during admission      |
| Mortality (unplanned) 30-day post-discharge |

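### The primary remote vs in-person model adjusts for a HOSPITAL score taken only at discharge, after randomisation and after every in-episode adverse event

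*Protocol*

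**What the plan says.** In the protocol's statistical methods, the section on remote vs in-person physician care defines the primary outcome as "number of adverse events during the acute episode of care" and analyses it with a "generalized linear model using Poisson distribution", clustered by physician through estimating equations. The adjustment set is PRISMA-7, age, gender, race/ethnicity, "education, and HOSPITAL score". The same paragraph says "we are cognizant of over adjustment" and allows further covariates only where the groups differ at baseline.

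The Covariates of Interest table lists the score as "Readmission risk score on discharge (HOSPITAL", with Discharge as the only day obtained. No admission version is defined anywhere in the protocol.

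Treatment Assignment randomises patients to remote care "versus in-person care (control) at the time of enrollment".

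The table that summarises adverse events includes one item that falls after discharge: "Mortality (unplanned) 30-day post-discharge".

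For home hospital vs traditional hospital, the propensity weighting is specified as "adjusting for covariates of interest (see table above), baseline functional status, and DRG". The early-transfer and paramedic analyses reuse that method.

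**The concern.** A covariate in a randomised comparison should be fixed before assignment. Otherwise it may lie on the path from treatment to outcome or, as here, downstream of the outcome itself. If a patient who has an adverse event leaves with a higher readmission-risk score, the score carries information about the event count. Conditioning on it then credits to the score part of a difference that belongs to the arm.

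In a superiority trial that would usually cost power. In a non-inferiority trial it makes a false claim of non-inferiority more likely. The outcome here is safety, and Treatment Assignment says that remote care continues as a single arm if it is found non-inferior.

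The choice also conflicts with the section's own stance on over-adjustment and baseline differences, because a discharge score is not a baseline variable.

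**Working it through.** **Step 1. Order of measurement, from the protocol.**

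| Item | When | Where |
|---|---|---|
| Randomisation | Enrolment | Treatment Assignment |
| Age, gender, race/ethnicity, education, PRISMA-7 | Admission | Covariates of Interest |
| In-episode adverse events | Enrolment to discharge | Remote vs In-Person Physician Care |
| HOSPITAL score | Discharge only | Covariates of Interest |
| Unplanned 30-day mortality | After discharge | Summarizing Adverse Events |

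HOSPITAL is the only one of the six adjusters that is not an admission variable.

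**Step 2. The plan's design figures** (Power analysis). The control rate is 0.09 events per patient (SD 0.29), the margin 0.1 events (0.09 to 0.19), alpha 0.025 and power 80%. The stated size is 105 per arm before and 130 per arm after clustering. With n = 2 × SD² × (z for alpha + z for power)² / margin²:

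- alpha 0.025: 2 × 0.0841 × (1.960 + 0.842)² / 0.01 = 132.0, rounded up to 133 per arm;
- one-sided 0.05: 2 × 0.0841 × (1.645 + 0.842)² / 0.01 = 104 per arm (105 with a t-based calculation).

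The stated 105 thus follows from one-sided 0.05, not from 0.025. That is a separate matter. I keep 130 per arm and the 0.025 level as stated.

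**Step 3. Model for the check.** Truth is set at the margin: 0.09 vs 0.19, a ratio of 0.19/0.09 = 2.11. Assumptions not in the protocol:

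- a standardised baseline score B with a rate ratio of 1.3 per SD;
- discharge score D = B + k × (number of events) + a × (remote arm) + noise of SD 0.5;
- k, the SDs that one event adds, ranges from 0 to 2, and a = 0 at first.

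The event count is regressed on arm and D in a Poisson model. Non-inferiority is declared when the log ratio + 1.96 SE is below ln(2.11) = 0.747. Large-sample estimates use 400,000 per arm. Error rates use 130 per arm and 4,000 trials, for a simulation error of about √(0.026 × 0.974 / 4,000) = 0.25 percentage points.

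**Step 4. Results with a = 0.** The difference column comes from this model. The ratio and error columns give the range over several variants: robust or model-based standard errors, and a score with or without noise.

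| k (SD per event) | Estimated ratio (true 2.11) | Estimated difference (true 0.10) | False non-inferiority |
|---|---|---|---|
| 0 | about 2.1 | 0.099 | 2-3% |
| 0.5 | 2.02-2.05 | 0.096 | 3-4% |
| 1 | 1.77-1.84 | 0.082 | 5-8% |
| 2 | 1.43-1.49 | 0.049 | 13-26% |

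The upper ends come from robust standard errors, which estimating equations normally use; the 13% comes from model-based ones. Adjusting for B alone gives ratios of 2.09-2.13 and 2-3% false non-inferiority at every k. Testing the absolute difference against 0.1 with robust errors gives nearly the same picture: 3.3%, 4.0%, 7.7% and 25.7% down the table, against 3-4% with B alone.

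**Step 5. A direct effect of arm on the score.** With k = 0.5, if remote care lowers the score by 0.25 SD (a = -0.25), the estimated ratio is about 2.36, away from the null and against non-inferiority. If it raises the score by 0.25 SD, the ratio is about 1.73-1.77.

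**The case against.** The strongest reply is that the size rests wholly on an assumption. The protocol does not list the score's components or say how far an event moves it. At 0 SD per event there is no bias, and up to 0.5 SD there is little. Serious inflation needs 1 SD or more, and the counted events include hypokalemia and thrombophlebitis at an IV site, for which nothing in the protocol supports so large a shift. That stands, and it is why the figures are given as a range that starts at zero.

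The check is also not the protocol's exact test. The margin is absolute and was converted to a ratio, although the difference scale gives a similar answer. Physician clustering is not modelled. Nor is the interim futility rule, which uses the raw arm difference and so is untouched by the covariate. In a variant without noise in the score, that rule lowered false non-inferiority at 2 SD from 17.9% to 13.5%. These points qualify the percentages, not the timing error.

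A reader might infer three stronger things that the protocol does not support:

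- **That the bias always favours non-inferiority.** It does so if only events move the score. Step 5 shows that an arm effect on the score can reverse it.
- **That the score follows the whole outcome.** The 30-day mortality item comes later.
- **That the propensity models use a 30-day caregiver-burden reading.** The table lists that measure at admission and at +30 days. An admission value exists, and nothing says the later one is used.

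The propensity section's own caution on over-adjustment is tied to sample size, not timing, so it does not exclude the discharge score.

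**Conclusion.** Wrong as written. The primary safety analysis conditions on a variable measured after randomisation and after every in-episode event, and the protocol offers no baseline version of it. This rests on the text alone and is firm.

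The size and direction of the bias are not fixed by the protocol. If events raise the score and the arm has no separate effect on it, the bias runs towards non-inferiority: negligible up to about 0.5 SD per event and material from 1 SD. Because the protocol gives no means of knowing where the truth lies in that range, the covariate should not stay in the primary model.

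The propensity models take in the same score through the covariate table. That follows from the text too, but no size was calculated for those analyses.

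**What to change.** In the remote vs in-person section, remove the discharge HOSPITAL score from the primary model and state that all adjusters are fixed before randomisation. If a measure of utilisation risk is wanted, the covariate table already collects at admission the number of admissions in the previous year, ED visits in the previous 6 months, and comorbidities. These are also available for patients who die or are transferred back before an ordinary discharge. The alternative is to define and collect an admission version of the score. Any model with the discharge score should be labelled a sensitivity analysis only.

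In the home hospital vs traditional hospital section, limit the propensity covariates to admission readings, which excludes the discharge score. The same limit then carries over to the early-transfer and paramedic analyses.

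The cost is a wording change. No new data are needed unless the admission version of the score is chosen.

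### The primary non-inferiority model omits the diagnosis stratum used for randomisation and lets baseline significance tests decide on extra covariates

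*Protocol*

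**What the plan says.** Protocol, Treatment Assignment: allocation uses "random sized blocks between 3 and 6 stratified by infection, heart failure, COPD/asthma, and other with concealed allocation".

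Protocol, Remote vs In-Person Physician Care: "The primary outcome (dependent variable) is number of adverse events during the acute episode of care". For the analysis, "We will assess the non-inferiority of the primary outcome with a generalized linear model using Poisson distribution", and "We will therefore cluster by Home Hospital physician using general estimating equations".

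On covariates the section first gives a caution: "Although we have multiple covariates of interest, we are cognizant of over adjustment". It then fixes a list: "We plan to adjust for age, gender, race/ethnicity, PRISMA-7", followed by education and the HOSPITAL score. Neither diagnosis nor randomisation stratum is on it. The list ends with an option: "We may include additional covariates if groups have significant differences at baseline". No candidate list, significance level or definitive version of the model is given.

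Elsewhere in the protocol's statistical methods, diagnosis enters only the home versus traditional hospital comparison (DRG in the propensity weights, and diagnosis subgroups), the plan that the early-transfer and paramedic analyses reuse. It does not enter this trial's primary model.

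**The concern.** Two things are out of line with good practice.

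First, the design treats diagnosis group as important enough to balance by stratification, and the analysis then drops it. An analysis should reflect how patients were allocated. A robust standard error that ignores the strata also carries between-stratum variation that the design has already removed from the comparison.

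Second, under concealed random allocation a significant baseline difference is a chance event. A test for it says nothing about whether the variable predicts adverse events. Using it to choose covariates makes the primary model depend on the data. Because the wording is permissive, two analysts could follow it faithfully and report different primary estimates from the same trial. In a non-inferiority trial with few events, a modest shift can matter when the confidence limit lies near the margin.

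**Working it through.** The plan states no figure for this point, so there is nothing of its own to reproduce. The checks below size each part.

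**Inputs from the protocol.** Control mean 0.09 events per patient and 260 patients after allowing for clustering (Power analysis, Remote vs In-Person Care Analysis); four strata (Treatment Assignment); 25 variables in the Covariates of Interest table, of which six are in the model, leaving 25 − 6 = 19.

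**Assumptions not in the protocol.** Baseline tests at 5% and independent; stratum shares 40/20/20/20%; stratum event rates as shown; robust (sandwich) variance, as is usual with estimating equations.

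**1. Chance that the rule is triggered.** With k independent tests and perfect randomisation, P(at least one hit) = 1 − 0.95^k.
- k = 19: 1 − 0.95^19 = 0.62
- k = 10: 1 − 0.95^10 = 0.40
- k = 4: 1 − 0.95^4 = 0.19

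**2. Effect of a triggered rule.** The trial was simulated with 260 patients, allocation balanced within strata, a Poisson log-link model with robust standard error, 2,500 runs per scenario and no physician clustering. Three of the 19 covariates were assumed prognostic (log rate ratio 0.3 per SD).
- At least one covariate was selected in 61-65% of runs.
- In those runs the log rate ratio moved with an SD of about 0.08-0.09, and in one run in ten by more than about 0.12-0.15. As exp(0.12) = 1.13 and exp(0.15) = 1.16, that is a 13-16% change in the rate ratio.
- The standard error was about 0.36-0.45, so a typical shift is about a fifth of a standard error.
- With the true rate ratio at 0.19/0.09 (the protocol's two rates expressed as a ratio margin), false non-inferiority with the rule in use was 2.5-2.6%, against a nominal 2.5%.

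**3. Effect of omitting the stratum.** Without strata, the robust variance is inflated by 1 + Var(stratum rate)/mean rate. For rates 0.05, 0.16, 0.06, 0.13 the mean is 0.4×0.05 + 0.2×(0.16 + 0.06 + 0.13) = 0.09. The variance is 0.4×0.04² + 0.2×(0.07² + 0.03² + 0.04²) = 0.00212. The ratio is 1 + 0.00212/0.09 = 1.0236, and its square root is 1.012.

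| Stratum rates | Variance ratio | SE ratio |
|---|---|---|
| equal | 1.000 | 1.000 |
| 0.069, 0.138, 0.069, 0.104 (2-fold) | 1.009 | 1.004 |
| 0.05, 0.16, 0.06, 0.13 (about 3-fold) | 1.024 | 1.012 |
| 0.03, 0.27, 0.03, 0.09 (9-fold) | 1.096 | 1.047 |

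The empirical SD of the estimate was the same without and with strata: 0.454 and 0.454 (equal rates), 0.448 and 0.448 (3-fold), 0.470 and 0.470 (9-fold). Only the reported standard error differs. Simulated power against the ratio margin went from 42.5% to 42.9%, 42.2% to 43.6% and 39.6% to 43.5%. These figures serve to compare the two models and are not an estimate of the trial's power. False non-inferiority was 2.5-2.7% without strata and 2.7-3.2% with them; the simulation error is √(0.025×0.975/2500) = 0.3 percentage points.

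**4. Room for parameters.** Expected events are 0.09 × 260 = 23.4. Intercept, arm and six covariates need at least 8 parameters; about 11 is plausible once categories are coded (assumed). That is 23.4/8 = 2.9 down to 23.4/11 = 2.1 events per parameter. Three stratum terms bring it to 23.4/11 = 2.1 down to 23.4/14 = 1.7.

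**The case against.** The best defence is that little harm can be shown. The extra adjustment is optional and comes on top of six named covariates and an explicit caution about over-adjustment. The 62% needs all 19 variables tested, at a level the protocol does not state, as if independent; several are plainly related, such as comorbidities, number of medications, prior admissions and emergency visits. The strata add almost nothing to the precision of a log-link Poisson model when the arms are balanced within them. Three more terms also sit awkwardly with so few events. Finally, the handling of strata is often settled in a statistical analysis plan, which is not at hand.

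Most of this stands, and it limits the point. A reader might infer that the primary model will change by chance in most such trials. The protocol makes adjustment a possibility and not a rule, and 62% is an upper scenario. A reader might also take the strata to be prognostic by construction, because the Safety table puts new arrhythmia, hypokalemia and acute kidney injury under a heart failure heading. The table that defines the primary outcome, Summarizing Adverse Events, counts them without that restriction, and no stratum event rates are given. Diagnosis is plausibly prognostic, no more.

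The defence does not reach the baseline-test sentence. That is stated text, and an analysis plan faithful to the protocol would carry it forward. The named covariate list, too, is stated and leaves out the stratum.

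**Conclusion.** The point holds as an inexpensive improvement. The stratum used in allocation is missing from the stated primary model, and a stated option allows covariates to be chosen on chance imbalance after data are seen. The main harm is a primary estimate that is not fixed in advance. The chance of a trigger runs from 19% to 62% depending on how many variables are tested, and a typical resulting shift is about a fifth of a standard error under the simulation's assumptions.

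The stratum half is mainly a matter of matching analysis to design. The excess in the robust standard error is 0-1% for up to 3-fold differences between strata and about 5% at 9-fold, and the required sample size does not change materially. Two stronger conclusions are tempting and unsupported: that the omission forfeits substantial precision or power, and that the baseline-test rule inflates type I error. All sizes rest on assumed stratum shares and rates, an assumed 5% test level and independent covariates, and they ignore clustering by physician.

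**What to change.** In Remote vs In-Person Physician Care:
- Add the four-level randomisation stratum to the primary model as a fixed effect.
- Delete the sentence on significant baseline differences.
- Fix the complete covariate list in advance, using only variables known at admission. The HOSPITAL score does not qualify as recorded: the Covariates of Interest table has it obtained at discharge.
- Report any further adjustment as a sensitivity analysis.

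This changes wording only and leaves conduct and data collection alone. The cost is three more parameters with about 23 expected events, which can be offset by shortening the covariate list. Which covariates to drop is the sponsor's choice.
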